## Abstract

**Background:**

Non-suicidal self-injury (NSSI) is a transdiagnostic behaviour that can be difficult to treat; to date no evidence based treatment for NSSI exists. Mindfulness Based Cognitive Therapy (MBCT) specifically targets the mechanisms thought to initiate and maintain NSSI, and thus appears a viable treatment option. The aims of the current study are to test the ability of MBCT to reduce the frequency and medical severity of NSSI, and explore the mechanisms by which MBCT exerts its effect.

**Methods/Design:**

We will conduct a parallel group randomised controlled trial of Mindfulness Based Cognitive Therapy (MBCT) versus Supportive Therapy (ST) in young people aged 18–25 years. Computerised block randomisation will be used to allocate participants to groups. All participants will meet the proposed DSM-5 criteria for NSSI (i.e. five episodes in the last twelve months). Participants will be excluded if they: 1) are currently receiving psychological treatment, 2) have attempted suicide in the previous 12 months, 3) exhibit acute psychosis, 4) have a diagnosis of borderline personality disorder, or 5) have prior experience of MBCT. Our primary outcome is the frequency and medical severity of NSSI. As secondary outcomes we will assess changes in rumination, mindfulness, emotion regulation, distress tolerance, stress, and attentional bias, and test these as mechanisms of change.

**Discussion:**

This is the first randomised controlled trial to test the efficacy of MBCT in reducing NSSI. Evidence of the efficacy of MBCT for self-injury will allow provision of a brief intervention for self-injury that can be implemented as a stand-alone treatment or integrated with existing treatments for psychiatric disorders.

**Trial registration:**

Australian New Zealand Clinical Trials Registry Number ACTRN12615000023550. Registered 16 January 2015.

## Background

Non-suicidal self-injury (NSSI), the deliberate destruction or alteration of body tissue without conscious suicidal intent and for purposes not socially sanctioned [1], is a transdiagnostic behaviour that is used to cope with intense emotions and psychological distress. Equally common among males and females, NSSI can include cutting, burning or carving the skin and hitting or banging the self or hard objects. Although typically emerging in adolescence, NSSI is most prevalent among 18–24 year olds (20 % lifetime history) [2]. NSSI differs from suicidal behaviour (including ideation and attempts) in being more prevalent, engaged in more frequently, typically involving non-lethal methods, and being driven by emotion regulation rather than a desire to end life. As such the aetiology of NSSI is markedly distinct from suicidal behaviour, necessitating a tailored treatment approach [3, 4].

In Australia, the direct hospital costs of non-suicidal self-injury are estimated at over $14 million per month [2]. Among 15–24 year olds, 7301 were hospitalised for self-harm (including suicidal behaviour) in 2009–2010, placing the direct cost in this age group alone at almost $34 million per year [5]. With increased awareness and efforts to improve help-seeking [6], these costs are set to rise dramatically unless effective interventions to minimise the frequency and medical severity of the behaviour are made available. Young people who self-injure carry a fourfold risk of suicidal thoughts and behaviours within the following year [7], and Australians who self-injure are 42 times more likely to attempt suicide [2]. Reducing the major risk factor of self-injury is crucial to suicide prevention efforts yet there is no targeted evidence-based treatment for self-injury.

Growing recognition of the prevalence and impact of NSSI has led to its inclusion in Section 3 of the latest edition of the *Diagnostic and Statistical Manual of Mental Disorders* (DSM) [8], as a condition for further study. Proposed criteria include: NSSI on five or more days in the past year, for the purpose of relief from negative feelings, resolving interpersonal difficulties or to induce a positive state (e.g. euphoria). NSSI is defined as being associated with negative thoughts and feelings, premeditation and rumination. The proposed criteria evidence discriminant validity [9–11].

Commensurate with the affect-regulatory function of NSSI, mechanisms thought to increase risk of NSSI in the face of stress include poor emotion regulation, poor distress tolerance and rumination on negative thoughts and feelings. Emotional cascade theory proposes that through rumination even minute emotional stimuli become amplified over time [12] and, in the absence of adaptive emotion regulatory strategies, individuals self-injure to escape the subsequent cascades of intense emotion. Supporting this, researchers consistently demonstrate increased arousal and rumination prior to NSSI [13, 14], higher physiological reactivity and poor distress tolerance when under stress [15], and emotional relief and reduced arousal after NSSI [16].

### Treatment for NSSI

Despite the adverse outcomes for people who engage in NSSI, there is no empirically validated treatment available [17]. Where NSSI is an outcome variable of interest in clinical trials, treatment has been exclusively designed for people with Borderline Personality Disorder (BPD) [18–20]. Given the transdiagnostic nature of NSSI, treatments that address NSSI beyond BPD are essential. Mindfulness-Based Cognitive Therapy (MBCT) was designed specifically to impact on attention to negative thoughts and images, emotion regulation, distress tolerance and rumination [21, 22], and successfully evidences reductions in emotional reactivity [23]. That this treatment directly addresses proposed diagnostic features of NSSI, and core mechanisms repeatedly implicated in NSSI [8], offers immense promise for MBCT as a treatment for NSSI. Yet, despite recent work implicating a lack of mindfulness in the maintenance of NSSI [24], no prior research has explored the ability of MBCT to impact the frequency and medical severity of NSSI. Garnering support for MBCT as a viable and efficacious treatment is essential to the on-going effort to reduce the impact and burden of NSSI.

If, as theorised, MBCT exerts its effect by minimising attention on negative thoughts and rumination, improving distress tolerance and emotion regulation, and reducing perceived and physiological stress responses, changes in these variables should be evident upon completion of an MBCT program, with subsequent improvement in NSSI. Assessing mechanisms of change is crucial to determining the ‘active ingredient’ in MBCT, facilitating optimal outcomes and tailored treatment approaches [25].

### The current study

In this study we aim to: 1) determine the efficacy of group Mindfulness Based Cognitive Therapy (MBCT) in decreasing the frequency and medical severity of Non-Suicidal Self-Injury (NSSI) among young people, relative to group Supportive Therapy (ST); and 2) establish the mechanisms by which MBCT reduces frequency and severity of NSSI. The following hypotheses are proposed:We expect MBCT to reduce the frequency and medical severity of NSSI, relative to ST and this reduction to be maintained at 3 month and 6 month follow-upWe expect MBCT to increase mindfulness, reduce rumination, improve emotion regulation, improve distress tolerance, reduce bias for negative stimuli, and reduce stress (self-reported and physiological, based on cortisol)We expect the proposed mechanisms of action will mediate the relationship between assigned treatment group and outcomes of reduced NSSI, lower scores on the Beck Anxiety Inventory, and lower scores on the Beck Depression Inventory-II (Fig. 1).

**Fig. 1 Fig1:**
[figure not shown]
Hypothesised model

## Methods/Design

### Study design

We will conduct a parallel group randomised controlled design in which half our participants receive Group Mindfulness Based Cognitive Therapy and half receive Group Supportive Therapy. We will implement a computerised block randomisation procedure to ensure equal distribution of participants across conditions (Fig. 2). As far as practically possible participants will be blind to group allocation. Self-report, behavioural and physiological measures will be administered at pre-treatment, mid-treatment, post-treatment, and 3 and 6-month follow-up. To maximise external validity, a minimum follow-up period of 6 months is recommended and will be adopted in the present study [26]. Baseline assessments and follow up assessments will be conducted by a researcher blind to group allocation.

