### Participants and recruitment

We will recruit 96 participants (48 per group) via our existing referral networks of GPs, mental health professionals, and university counselling services, as well as through advertising in print media and social network sites. Inclusion criteria include: 1) Aged 18–25 years, and 2) meet proposed DSM-5 criteria for NSSI [8]. Participants will be excluded if they: 1) are currently receiving psychological treatment, 2) have attempted suicide in the previous 12 months, 3) exhibit acute psychosis, 4) have a diagnosis of borderline personality disorder (BPD), or 5) have prior experience of MBCT. As NSSI is one diagnostic criterion for BPD, young people diagnosed with BPD will be excluded to avoid confounding diagnosis and behaviour. Individuals presenting with suicidal behaviour, psychosis or BPD will be appropriately referred.

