### Intervention

A trained psychologist will conduct telephone interviews to assess eligibility with the single-item Clinician-Rated Severity of Non-Suicidal Self-Injury [27] and 6-item Mini International Psychiatric Interview [28]. Both treatment conditions will comprise 8 weekly group sessions of 2 h duration with up to 12 participants in each group. All group sessions and assessments will occur at the Curtin University Psychology Clinic. As per standard practice, two trained therapists, blind to the results of baseline and follow-up assessments, will facilitate each group. Suicidality will be monitored weekly throughout treatment (both conditions) using the 3-item Self-Monitoring Suicide Ideation Scale [29].

To ensure treatment fidelity, each therapist will receive training and weekly supervision. All treatment groups will be audiotaped with 10 % checked to ensure adherence to manualised treatment protocols, using the Mindfulness Based Cognitive Therapy Adherence Scale for MBCT group [30]. At the first treatment session all participants will complete the 6-item Credibility/Expectancy Questionnaire [31] to assess treatment face validity. We will assess treatment acceptability using Dear et al’s [32] 4-item acceptability rating scale. Upon completion of treatment, participants will also provide open comments about acceptability, and specify intended NSSI prevention strategies.

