##### Clinician-rated severity of Non-suicidal self-injury

[27]: This single item scale assesses the severity of NSSI on a scale of 0 = None; 1 = Sub-threshold; 2 = Mild; 3 = Moderate; and 4 = Severe. The measure was designed to capture clinically meaningful changes in NSSI severity, based on the proposed DSM-5 criteria [8]. Therapists will rate each participant at the end of each therapeutic session.

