### Sample size calculation and statistical analysis

We will perform both Intention to Treat and Per Protocol analyses. We will conduct a sensitivity analysis [54], and compare complete cases versus cases lost to follow-up on baseline characteristics and scores on clinical measures, by randomization group [55]. Mixed Model Repeated Measures analyses will compare results on outcome measures across conditions and time points, while controlling for random effects (e.g. age, gender). Using medium effect sizes [56] 40 per group are required for power = .80 and α = .05 (G*Power) [57]. Recruiting an additional 20 % (*n* = 48 per group) will allow for typical dropout [58, 59]. Mechanisms of action (see Fig. 1), will be tested using multiple mediational analysis with 1000 bias-corrected bootstrap samples in MPlus, to test total and specific indirect effects. This powerful test of mediation requires a sample of 71 participants to detect a medium effect [60]. Participants will be classified into outcome categories (Recovered, Improved, Unchanged, Deteriorated) [61] according to Reliable Change Index and Clinical Significance of change at post-treatment and follow-up, to determine whether MBCT and ST differ in clinically significant reductions in NSSI and associated symptoms of anxiety and depression over time.

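### The NSSI severity rating obtained before allocation has no stated use in the randomisation or the model; naming it as a baseline covariate would be a cheap gain in precision

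*Protocol article*

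**What the plan says.** All references are to the protocol article.

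- **Allocation (Study design).** "We will implement a computerised block randomisation procedure to ensure equal distribution of participants across conditions". The ratio is 1:1: "half our participants receive Group Mindfulness Based Cognitive Therapy and half receive Group Supportive Therapy". Neither this section nor the abstract names a stratification factor.
- **Size (Participants and recruitment).** "We will recruit 96 participants (48 per group").
- **Screening (Intervention).** A psychologist conducts "telephone interviews to assess eligibility with the single-item Clinician-Rated Severity of Non-Suicidal Self-Injury". The item is graded "0 = None; 1 = Sub-threshold; 2 = Mild; 3 = Moderate; and 4 = Severe". Because it serves to establish eligibility, it is available for everyone before allocation.
- **Adjustment (Sample size calculation and statistical analysis).** The mixed model compares conditions and time points "while controlling for random effects (e.g. age, gender"). NSSI at entry is not among the examples.
- **Other NSSI measurements.** The diary runs through the trial without a stated pre-treatment period. During treatment, therapists give the clinician rating after each session, so its first in-trial value follows session 1. Study design speaks of pre-treatment administration of the measures in general, which may or may not include an NSSI count.

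**The concern.** Blocks equalise the number of people per arm. They do nothing for how severely or how often those people self-injure. The primary outcome is NSSI frequency and medical severity, and entry sets a floor of five episodes in a year with no stated ceiling, so participants may differ widely at the start. The screening rating is the only NSSI measurement that the article explicitly places before allocation, and no use of it beyond eligibility is described.

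Two things are at stake. The first is precision: variation in the outcome that entry severity could explain stays in the error term. The second is credibility: in a trial of 96, a visible difference in NSSI at entry invites doubt about either a positive or a null result, and the article names no adjustment that answers it.

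**Working it through.** **1. The plan's own figures.** The article states "Using medium effect sizes [56] 40 per group are required for power = .80 and α = .05 (G*Power") and then "Recruiting an additional 20 % (*n* = 48 per group) will allow for typical dropout". The second follows from the first: 40 × 1.20 = 48, which covers a loss of 8/48 = 16.7%. No numerical effect size is given. A repeated-measures ANOVA between-groups test with f = 0.25 and a within-person correlation of 0.5 gives a total of 82 with four measurements and 78 with five, so 80 (40 per arm) is consistent with that reading. The sample size is not in dispute here; it supplies the 48 per arm used below.

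**2. Chance imbalance at entry.** For a standardised baseline variable under 1:1 allocation, SE = √(2/48) = 0.204, and P(|difference| > c) = 2 × [1 − Φ(c/0.204)].

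| c (SD) | Probability |
|---|---|
| 0.20 | 33% |
| 0.25 | 22% |
| 0.40 | 5% |
| 0.50 | 1.4% |

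This needs no assumption about the spread of NSSI beyond approximate normality of the difference in means.

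**3. Imbalance in the raw rate.** The article gives no mean, SD or dispersion for NSSI. Assuming log-normal rates and blocks of four (4,000 simulated trials per setting), the chance that arm means differ by more than 1.25-fold is 4%, 24%, 38%, 50% and 64% at log-SD 0.5, 0.8, 1.0, 1.2 and 1.5. The answer is governed almost entirely by an unknown.

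**4. Validity.** With n = 96 and true effects of 0 and 0.5 SD, the mean estimate was within 0.005 SD of the truth, and type I error was 0.038 to 0.057, with or without stratification.

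**5. What stratification does for balance.** With a three-level rating correlated 0.5 with the log rate, the 1.25-fold risk moves from 24% to 20% at log-SD 0.8, from 38% to 35% at 1.0 and from 64% to 62% at 1.5. At log-SD 1.0 the 1.3-fold risk moves from 30% to 28% at correlation 0.5, and from 31% to 20% at 0.9. A large reduction needs a rating that nearly reproduces frequency.

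**6. What adjustment does for power.** Take a continuous baseline measure with correlation ρ to follow-up, d = 0.5, n = 96 and unstratified blocks:

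| ρ | Unadjusted | Change score | Baseline-adjusted |
|---|---|---|---|
| 0.3 | 0.68 | 0.54 | 0.72 |
| 0.5 | 0.67 | 0.68 | 0.79 |
| 0.7 | 0.67 | 0.87 | 0.91 |

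At ρ = 0.5, adding stratification to adjustment leaves power at 0.79. Comparing change from baseline does not replace adjustment, and at ρ = 0.3 it is worse than no adjustment.

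**7. What the screening rating itself can deliver.** It is one coarse item, so the gain is smaller than with a continuous baseline. The variance removed cannot exceed about r², where r is the assumed correlation with the log NSSI rate; grouping into levels and noise in the later counts take it lower.

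| r | Ceiling r² | Simulated reduction |
|---|---|---|
| 0.3 | 9% | 0-1% |
| 0.5 | 25% | 5-9% |
| 0.7 | 49% | 14-20% |
| 0.9 | 81% | 22-38% |

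A repeat simulation gave reductions of similar size on log-transformed counts. On raw counts the gain was smaller at the higher correlations. Stratifying on top of this adjustment adds little.

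**8. Why a covariate-by-time term.** If pre-treatment is one of the modelled time points, a main effect of the rating shifts every time point by the same amount. It cancels from post minus pre, so with complete data the change-from-baseline contrast is unchanged. The rating must be allowed a different slope at each time point, or the model must take only post-baseline values as outcomes.

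**The case against.** The strongest reply is that nothing here is wrong. The allocation sentence promises equal numbers, and blocks deliver them. Unstratified 1:1 blocks are a valid design. The article condenses a fuller protocol, in which strata may be named, and the allocation figure is not shown. The covariates are given as examples, so the list is open. Pre-treatment measurement is planned, and the repeated-measures model can take in starting level. Finally, any gain from a single coarse item, narrowed further by eligibility, may be slight.

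All of this stands against calling it an error. It does not remove the suggestion. A pre-treatment NSSI count is not spelled out, and a change-from-baseline contrast does not recover what covariate adjustment does (step 6).

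A reader might infer more: that the NSSI rate is known to be highly uneven, that the arms will therefore often start unequal on the primary outcome, and that stratifying would largely cure this. The article does not support that. It gives no dispersion; unevenness is an inference from an uncapped entry rule. The frequency of imbalance runs from 4% to 64% over plausible spreads (step 3), and stratifying on this item removes little of it unless the item closely tracks frequency (step 5). Nor would chance imbalance bias the estimate.

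**Conclusion.** A cheap improvement to the plan, not a fault in it. As described, allocation balances numbers only, the named adjustment examples omit NSSI at entry, and a pre-allocation severity rating has no stated use after eligibility. About 22% of trials of this size would show a difference above 0.25 SD on any given baseline NSSI measure. The consequence is lost precision and weaker credibility, with no bias and no inflation of type I error.

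The recoverable variance ranges from practically nothing (r = 0.3) to 22-38% (r = 0.9), nearly all of it through adjustment. These figures rest on assumed log-normal rates, blocks of four, a grouped rating and a correlation that the article does not report. The 22% rests only on 48 per arm.

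**What to change.** In the model that compares post-baseline NSSI between arms, prespecify the screening clinician-rated severity as a fixed baseline covariate. Add pre-treatment NSSI frequency if it is collected. If pre-treatment remains a time point in the model, include the covariate-by-time interaction as well.

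Optionally, stratify the computerised blocks by two levels of the same rating and keep that stratum in the model. Two levels suffice, since eligibility should leave few participants at the bottom of the scale.

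The cost is one or a few model terms using data already gathered. If stratification is added, it also needs a setting in the randomisation program, and incomplete blocks may leave therapy groups within a recruitment wave slightly uneven in size.

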**Fig. 2 Fig2:**
[figure not shown]
CONSORT flow diagram of participant allocation

### Participants and recruitment

We will recruit 96 participants (48 per group) via our existing referral networks of GPs, mental health professionals, and university counselling services, as well as through advertising in print media and social network sites. Inclusion criteria include: 1) Aged 18–25 years, and 2) meet proposed DSM-5 criteria for NSSI [8]. Participants will be excluded if they: 1) are currently receiving psychological treatment, 2) have attempted suicide in the previous 12 months, 3) exhibit acute psychosis, 4) have a diagnosis of borderline personality disorder (BPD), or 5) have prior experience of MBCT. As NSSI is one diagnostic criterion for BPD, young people diagnosed with BPD will be excluded to avoid confounding diagnosis and behaviour. Individuals presenting with suicidal behaviour, psychosis or BPD will be appropriately referred.

### Intervention

A trained psychologist will conduct telephone interviews to assess eligibility with the single-item Clinician-Rated Severity of Non-Suicidal Self-Injury [27] and 6-item Mini International Psychiatric Interview [28]. Both treatment conditions will comprise 8 weekly group sessions of 2 h duration with up to 12 participants in each group. All group sessions and assessments will occur at the Curtin University Psychology Clinic. As per standard practice, two trained therapists, blind to the results of baseline and follow-up assessments, will facilitate each group. Suicidality will be monitored weekly throughout treatment (both conditions) using the 3-item Self-Monitoring Suicide Ideation Scale [29].

To ensure treatment fidelity, each therapist will receive training and weekly supervision. All treatment groups will be audiotaped with 10 % checked to ensure adherence to manualised treatment protocols, using the Mindfulness Based Cognitive Therapy Adherence Scale for MBCT group [30]. At the first treatment session all participants will complete the 6-item Credibility/Expectancy Questionnaire [31] to assess treatment face validity. We will assess treatment acceptability using Dear et al’s [32] 4-item acceptability rating scale. Upon completion of treatment, participants will also provide open comments about acceptability, and specify intended NSSI prevention strategies.

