### Ethical issues

After initial telephone screening to assess eligibility, during which participants are verbally informed of the study requirements, all participants will be provided with a detailed information sheet which outlines the aims and participation requirements of the study, informs participants of the confidential and voluntary nature of participation, and outlines how data are to be collected, used and stored in accordance with relevant Privacy Legislation. All participants will be afforded the opportunity to ask questions about the study and will provide signed consent to participate in the research project. Participants are free to withdraw from the research project at any time.

There is some concern regarding the potential for social contagion when discussing NSSI in a group setting. Our experience and a growing evidence base, suggests that when appropriately addressed, iatrogenic effects are rarely observed [34]. Conversely, research indicates that participants benefit from being asked about their NSSI [35, 36]. We will minimise risk of iatrogenic effects by following established guidelines to reduce social contagion [37], including discouraging sharing of explicit details, NSSI images or scars in the group setting. This conduct of this trial has been approved by the Curtin University Human Research Ethics Committee (Ref number: 4884).

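### Both arms are treated in therapy groups, but the 80% power figure assumes independent participants and the described mixed model names no therapy-group term

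*Protocol article*

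**What the plan says.** All places are in the protocol article. No statistical analysis plan was available.

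- **Delivery.** Under Intervention, both arms have 8 weekly sessions "with up to 12 participants in each group", each group facilitated by two therapists.
- **Group interaction.** The MBCT section has members helping each other with crisis planning. The Supportive therapy section relies on discussion among members and presents ST as a control for social support. Ethical issues says: "There is some concern regarding the potential for social contagion when discussing NSSI in a group setting". It adds that harmful effects are seldom seen when the issue is handled properly, and lists precautions.
- **Size.** Participants and recruitment: "We will recruit 96 participants (48 per group"). The sample size section says "Using medium effect sizes", "40 per group are required for power = .80 and α = .05", and raises 40 to 48 for dropout ("Recruiting an additional 20" per cent). It gives no ICC, design effect or number of therapy groups.
- **Model.** "Mixed Model Repeated Measures analyses will compare results on outcome measures across conditions and time points", with age and gender as examples of the random effects controlled for.
- **Power claim.** The Discussion concedes that the sample is small but says the repeated-measures design gives enough power for medium effects on the primary outcome.

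**The concern.** Participants are randomised individually but treated together. Members of a therapy group share sessions, facilitators and peers, so their outcomes after treatment starts may be correlated. This is a design in which clustering arises through treatment, in both arms.

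Two things are at stake. The first is the validity of the main comparison: an analysis that ignores a positive within-group correlation gives confidence intervals that are too narrow and a false-positive rate above 5%. The second is the power claim, which the article fixes as a figure. Repeated measurement reduces noise within a participant; it does nothing about correlation between participants in the same therapy group.

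**Working it through.** **Inputs from the article:** two-sided alpha 0.05 (sidedness not stated, two-sided assumed), power 0.80, 40 evaluable and 48 recruited per arm, 5 assessment points, groups of at most 12. **Assumed:** medium effect as Cohen's f = 0.25, correlation between time points 0.5, ICC 0.01 to 0.10 on the scale of the contrast tested.

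**Step 1: reproduce the 40 per arm.** For the between-arm test in a repeated-measures ANOVA, the noncentrality is f² × N × m / (1 + (m − 1)ρ).
- N = 80: 0.0625 × 80 × 5 / (1 + 4 × 0.5) = 25 / 3 = 8.33. With 1 and 78 df, power is 81.4%.
- The smallest N reaching 80% is 78, or 39 per arm.

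So 40 per arm reproduces, under independence. The match depends on the assumed inputs: N is 58 at correlation 0.3 and 98 at 0.7. A simple two-sample comparison with d = 0.5 needs 63 per arm.

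**Step 2: number of therapy groups.** 48 / 12 = 4 per arm at least. With 40 completers, that is 10 per group. Since 12 is a ceiling, a second case uses 6 groups per arm: 48 / 6 = 8 recruited and 40 / 6 ≈ 6.7 completers each.

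**Step 3: effect of clustering.** With g completers per group:
- Design effect DE = 1 + (g − 1) × ICC.
- Standard error reported if clustering is ignored, relative to the correct one: 1/√DE.
- Actual two-sided error of a nominal 5% test: 2 × [1 − Φ(1.96/√DE)].
- Power for the effect that 40 independent participants per arm detect with 80% power in a t test (d = 0.634): shift = 0.634 × √(40/2) / √DE = 2.835/√DE. This is referred to the normal distribution, then to a noncentral t with (number of therapy groups − 2) df.

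Example, g = 10 and ICC 0.05: DE = 1 + 9 × 0.05 = 1.45; SE ratio 0.83; error 2 × [1 − Φ(1.628)] = 10.4%; shift 2.355; normal power 65%; with 6 df 51%.

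| Groups per arm | ICC | DE | SE ratio | Naive error | Power, normal | Power, group-level df |
|---|---|---|---|---|---|---|
| 4 of 10 (6 df) | 0.01 | 1.09 | 0.96 | 6% | 78% | 62% |
| | 0.02 | 1.18 | 0.92 | 7% | 74% | 59% |
| | 0.05 | 1.45 | 0.83 | 10% | 65% | 51% |
| | 0.10 | 1.90 | 0.73 | 16% | 54% | 41% |
| 6 of 6.7 (10 df) | 0.02 | 1.11 | 0.95 | 6% | 77% | 68% |
| | 0.05 | 1.28 | 0.88 | 8% | 71% | 62% |
| | 0.10 | 1.57 | 0.80 | 12% | 62% | 53% |

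Part of the loss in the last column is the price of few groups: with 6 df the same formula gives about 66% even at ICC 0. Using the noncentrality from Step 1 divided by DE instead of d = 0.634 changes the power figures by about one or two points. On that basis power drops below 80% at an ICC of about 0.004 (10 completers per group).

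**Step 4: which random effect protects the test.** The model compares arms across time from pre-treatment onward. Therapy groups do not exist at baseline, so clustering appears afterwards. A therapy-group random intercept that is constant over time cancels from a change-from-baseline contrast and so cannot absorb it. A small simulation agrees: in 200 null trials (pre and post, clustering only at post, ICC 0.10, 4 groups of 10 per arm), the error was 16.5% both with and without such an intercept. Some fits gave convergence warnings, and the Monte Carlo standard error is √(0.165 × 0.835 / 200) ≈ 2.6 points.

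**The case against.** **The model is not closed.** The random effects are given as examples, and an article usually leaves the full random-effects structure and df method to the analysis plan. This stands. A reader might infer that the plan excludes therapy group and that its standard errors are therefore too small; the article does not show that. It does show a power figure computed without clustering, which a later plan cannot correct by adding a model term, and example terms that are not clustering units.

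**The ICC is unknown.** This also stands. At ICC 0 the standard errors are right and the participant-level power holds; at 0.01 the participant-level loss is two or three points. The harm is conditional. The article's own account of group interaction makes zero an unsafe default.

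**The groups may not be closed or separately staffed.** A reader might picture fixed groups, each with a therapist pair of its own. The article says only that two therapists facilitate each group; the same pair could run several, or groups in both arms. The point needs only shared sessions and peers.

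**Contagion.** It is tempting to take the contagion remark as evidence of clustering in self-injury. The same paragraph says such effects are rarely seen when addressed. It supports considering clustering, not a particular ICC.

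**The dropout margin might absorb it.** Only if the ICC is very small and nobody drops out. With all 96 retained in groups of 12, the noncentrality is 0.0625 × 96 × 5 / 3 = 10. Participant-level power is 81% at ICC 0.02 (DE 1.22) and 71% at 0.05 (DE 1.55); with 6 df it is 67% and 57%.

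**Conclusion.** The point holds conditionally. The article states 80% power from 40 per arm with no allowance for therapy-group correlation, although both treatments are delivered in groups and use group interaction. If the ICC is positive and clustering is left out of the analysis, the nominal 5% error is about 6% to 16% for ICC 0.01 to 0.10 in the largest-group case. In the smaller-group case it is about 6% to 12% for ICC 0.02 to 0.10. A valid analysis with group-level df would have roughly 41% to 62% power in the first case and 53% to 68% in the second. These sizes rest on the assumed ICCs, the assumed group counts and an effect back-calculated from the stated power, since the article quantifies neither the effect nor the correlation between time points. It is not established that the eventual model omits therapy group. The unqualified power statement does need correcting, and the model should be specified before analysis.

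**What to change.** 1. Record a therapy-group identifier for every participant during the trial.
2. In each between-arm model, include therapy group nested in arm as a random effect that acts on the post-baseline contrast. Use either a group-by-time random effect or a baseline-adjusted model of post-baseline outcomes with a group random effect. Use Kenward-Roger or Satterthwaite df. A time-constant intercept alone is not enough, and a df correction does not replace a missing variance component.
3. Enter age and gender as fixed covariates.
4. Account for therapy group in the mediation models, and state that cluster-robust standard errors are unreliable with about 8 clusters.
5. Replace the unqualified 80% with power over ICC 0.01 to 0.10 and plausible group sizes, and qualify the Discussion's statement that power is sufficient.

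The cost is one data field, revised analysis wording, wider confidence intervals and a lower stated power. No added enrolment is asked for.
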